# Trial protocol: RadTARGET, a multicenter phase II randomized controlled trial evaluating focal radiotherapy boost with de-intensification of dose to non-suspicious prostate in patients with intermediate- or high-risk prostate cancer

**DOI:** 10.1016/j.ctro.2026.101184

**Published:** 2026-05-15

**Keywords:** Pelvic radiation therapy, Focal therapy, Tumor boost, Dose de-escalation, Quality of life, Genitourinary toxicity, Gastrointestinal toxicity, Diffusion MRI, Restriction spectrum imaging, PSMA PET

## Abstract

•Phase II trial compares tumor-focused vs standard RT in prostate cancer.•Image-guided RT boosts tumors and reduces dose outside of tumors.•Test if image-guided RT reduces acute GU/GI toxicity vs standard RT.•Target dominant lesion where most post-RT recurrences occur.•Results will inform phase III trial for efficacy and safety validation.

Phase II trial compares tumor-focused vs standard RT in prostate cancer.

Image-guided RT boosts tumors and reduces dose outside of tumors.

Test if image-guided RT reduces acute GU/GI toxicity vs standard RT.

Target dominant lesion where most post-RT recurrences occur.

Results will inform phase III trial for efficacy and safety validation.

## Introduction

Modern prostate radiation therapy (RT), with dose-escalation and focal boosting, has excellent oncologic outcomes for patients with intermediate- and high-risk prostate cancer (PC) [1], [2]. Dose escalation to the whole prostate comes at the expense of meaningful adverse events [3], [4], spurring efforts to advance RT delivery to maximize both disease control and safety. The landmark FLAME randomized trial provided high-level evidence that the addition of a focal boost to the MRI-defined tumor improved oncologic outcomes without increased adverse events or decreased quality of life, compared to standard dose to the whole prostate [1]. However, many patients undergoing standard dose to the whole prostate still experience short- and long-term adverse events that impact post-treatment quality of life. Given that patients typically live many years after definitive treatment for localized PC, there is interest in improving the therapeutic ratio of definitive RT for localized PC to minimize impact of treatment on long-term quality of life.

One way to improve the therapeutic ratio is by decreasing rates of adverse events. Side effects of RT are driven by radiation dose to neighboring organs of interest (NOIs; historically called organs at risk), particularly rectum and bladder for definitive prostate radiotherapy [5]. The urethra and penile bulb are also thought to be important [6], [7], [8]. While focal boosting maintains a high probability of tumor control, treatment-related side effects could potentially be reduced through tumor-focused RT. Patterns of failure analyses in the context of both focal boosting and non-focal boosting demonstrate that intra-prostate recurrences occur primarily at the location of the dominant tumor [9], [10], [11], [12]. Furthermore, the FLAME investigators demonstrated a clear dose–effect relationship: near-minimum dose to gross tumor volume (GTV) was associated with risk of PC recurrence [12], [13]. Thus, intra-prostatic recurrence is likely a consequence of undertreatment of the primary tumor rather than undertreatment of the remaining prostate gland, providing a premise for a new approach to focal boosting with tumor-focused RT whereby the tumor receives ablative-dose RT, and the rest of the electively irradiated prostate receives a de-escalated dose.

Accurate discrimination of clinically significant intra-prostate tumors from benign prostate tissue is a prerequisite for tumor-focused RT. Multiparametric magnetic resonance imaging (mpMRI) is the current standard for PC detection [14] and tumor delineation [15]. A quantitative imaging biomarker for PC – the Restriction Spectrum Imaging restriction score (RSIrs) – has been shown to be more specific than conventional mpMRI for clinically significant PC detection [16], [17], [18], [19]. Beyond MRI, positron emission tomography targeting the prostate-specific membrane antigen (PSMA PET) is now routinely used in staging of primary PC [20], and several studies report excellent performance for identification of intra-prostate tumors [21], [22], [23]. Furthermore, the combination of MRI and PSMA PET improve the sensitivity and specificity of intra-prostatic tumor delineation over each modality on its own [24], [25]. By utilizing these advanced biological imaging techniques, intra-prostatic tumors can be accurately delineated with confidence, allowing for tumor-focused RT.

Tumor-focused RT involves ablative-dose RT to the imaging-defined tumors, while de-escalating dose to the remainder of the electively irradiated prostate gland. Similar approaches are commonly used in definitive RT for non-prostate malignancies, such as head and neck cancers. Lack of discrimination on CT scans between normal prostate tissue and PC previously made tumor-focused RT infeasible for PC. However, with improvement in imaging allowing for discrimination of PC versus benign prostate tissue, tumor-focused RT could now be adopted to lower dose to NOIs and potentially increase safety and quality of life while preserving the excellent oncologic outcomes seen with current RT. Prospective data on this topic are scarce, and no randomized trials have been completed. There is one ongoing trial of MRI-guided RT dose de-escalation (DESTINATION) using a linear accelerator with onboard MRI (MR-linac) [26]. A pragmatic, randomized trial with standard linear accelerators is warranted to compare the safety and efficacy of tumor-focused RT to standard RT. We describe here the RAdiotherapy Dose TAiloRing Guided by Enhanced Targeting (RadTARGET) study, a multicenter phase II randomized controlled trial evaluating a tumor-focused strategy for PC radiotherapy (ClinicalTrials.gov NCT06990542). We hypothesize that tumor-focused RT will yield similar efficacy and substantially lower adverse events compared to standard prostate RT.

## Design

RadTARGET is a phase II, two-arm, randomized clinical trial evaluating tumor-focused RT versus standard-dose RT. Evaluation will be performed in terms of physician-reported adverse events, patient-reported safety, and oncologic outcomes. Participants will undergo RT for intermediate- or high-risk localized PC (Fig. 1). A dynamic allocation procedure is used to assign participants in a 1:1 ratio to receive either standard-dose RT or image-guided, tumor-focused RT. To minimize biased clinical decision-making based on randomization, treating physicians will declare the participant’s treatment plan prior to randomization. Each arm will be balanced for risk group (intermediate/high), fractionation type (stereotactic body RT [SBRT] / non-SBRT), duration of androgen deprivation therapy (ADT; none/short-term/long-term), bladder filling (full/empty), and spacer use (yes/no). The primary objective is to evaluate the relative merits of image-guided, tumor-focused RT vs. standard-dose RT for acute GU/GI adverse events in the setting of definitive RT for intermediate- and high-risk PC. The endpoint will be acute, any-attribution GU/GI grade ≥2 adverse events within 3 months of completing RT, compared between randomized arms. Adverse events will be defined using Common Terminology Criteria for Adverse Events (CTCAE) version 5.0 grading.

**Fig. 1 f0005:**
[figure not shown]
RadTARGET trial schema.

The study will enroll 150 participants at the University of California San Diego (UCSD), with completion of enrollment anticipated over 3 years. Inclusion and exclusion criteria are listed in Table 1. Participants must be ≥18 years old, have a diagnosis of intermediate- or high-risk localized PC, and plan to undergo curative-intent RT. They must also have one or more lesions visible on prostate MRI and/or PSMA PET with concordant pathology from biopsy needle locations. Participants with bilateral hip implants, prior PC treatment (including prostatectomy), or prior RT to the pelvis are not eligible. ADT may be started up to 90 days before randomization if study-compatible imaging was performed within 4 months of starting ADT. Participants must provide informed consent and be willing to comply with all study procedures for the duration of the study. This study was approved by UCSD’s Institutional Review Board (IRB) and ethics committee.

**Table 1 t0005:** Inclusion and exclusion criteria for the RadTarget trial. The study population is patients with intermediate- or high-risk prostate cancer planning to undergo definitive radiotherapy with or without systemic therapy.

RadTarget Trial Study Population
**Inclusion Criteria**
To be eligible to participate in this study, an individual must meet all of the following criteria:
• Provision of signed and dated informed consent form
• Stated willingness to comply with all study procedures and availability for the duration of the study
• Persons, aged at least 18 years
• Histologic confirmation of prostate adenocarcinoma with plan for curative-intent radiation therapy
• Lesion visible on prostate MRI and/or PSMA PET/CT (according to the treating physician) with concordant pathology from biopsy needle locations
• For participants able to cause a pregnancy: use of condoms or other methods to ensure effective contraception with partner during the radiation therapy treatment and for at least 6 months afterward.

**Exclusion Criteria**
An individual who meets any of the following criteria will be excluded from participation in this study:
• Bilateral hip implants
• Prior prostatectomy
• Prior prostate cancer treatment (e.g., focal therapy). Note that participants who started hormone therapy within the 90 days prior to randomization are eligible, as long as study-compatible imaging was performed within the 4 months prior to starting the hormone therapy.
• Prior radiation therapy to an area requiring treatment in the present study

### Treatment description

The study intervention is image-guided, ablative-dose RT to the sites of clinically significant, macroscopic tumors, while simultaneously de-escalating dose to areas of subclinical disease or benign prostate tissue within the rest of the electively irradiated prostate. All participants must have a pre-treatment MRI (consistent with PI-RADS v2.1 criteria [14]) with a multi-*b*-value diffusion-weighted MRI protocol compatible with calculation of the Restriction Spectrum Imaging restriction score (RSIrs) cancer biomarker. In RadTARGET, the treatment target (gross tumor volume [GTV]) will be manually delineated by the treating radiation oncologist using MRI with RSIrs +/- PSMA PET. Biopsy results and radiologist annotations that may be available should also be considered. For patients receiving ADT, the GTV should be delineated using pre-ADT images. Data collection and follow-up details are provided in the Supplemental Material and Supplemental Table 1.

### Experimental arm

For the experimental arm, clinical target volumes (CTV) are: *CTV_high*, defined as the GTV + 5 mm isotropic margin, cropped within prostate (with optional delineation of additional areas of moderate suspicion); and *CTV_low*, defined as the prostate +/- seminal vesicles (at the discretion of the treating physician). Elective pelvic lymph node RT (*CTV_LN*) is optional and at the discretion of the treating physician. Creation of planning target volumes (PTV) should follow UC San Diego Department of Radiation Medicine and Applied Sciences (RMAS) standards and guidelines, but adaptation is allowed at physician discretion or per local institutional standard practice. *PTV_high* is defined as *CTV_high* without additional margin. Doses for the various fractionations for the experimental arm are listed in Table 2. The dose covering ≥98% of the target volume (D98) for *CTV_high* for participants in the experimental arm must be at least standard of care prescription dose.

**Table 2 t0010:** Radiation doses for the experimental arm. Abbreviations: GTV, gross tumor volume (the visible tumor); CTV, clinical target volume (GTV with isotropic margin to cover areas at risk of microscopic disease); Gy, gray.

Fractionation	GTV	CTV_high	CTV_low	CTV_LN
Standard Fractionation (39–40 fx)	D98 up to 94 Gy	78–80 Gy in 39–40 fx	56 Gy in 28 fx	50.4 Gy in 28 fx
Moderate Hypofractionation (28 fx)	D98 up to 84 Gy	70 Gy	56 Gy	50.4 Gy
Moderate Hypofractionation (20 fx)	D98 up to 74 Gy	60 Gy	56 Gy	44 Gy
Stereotactic Body Radiotherapy (5 fx)	D98 up to 45 Gy	40 Gy	30 Gy	25 Gy

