### Control arm

As a pragmatic trial investigating image-guided, tumor-focused RT for intermediate- and high-risk prostate cancer, RadTARGET is not overly prescriptive for the control arm. Control arm definitive RT modality, dose, frequency, and administration must be in concordance with RMAS Standards and Guidelines or local institutional standard practice. Image-guided focal boost to MRI-visible disease is allowed and generally expected, but not required. For the control arm, the prostate CTV includes the entire prostate and receives the full prescription dose, corresponding to the relevant allowed fractionation scheme (i.e., *CTV_high* in Table 2). The proximal seminal vesicles may be included at physician discretion and would receive the *CTV_low* dose in Table 2.

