### Both arms

For both trial arms, all other CTV and PTV structures should conform to RMAS or local institutional standards and guidelines. NOIs should be delineated per RMAS guidelines or local institutional practice. The urethra must be delineated if a focal tumor boost is delivered. As a pragmatic trial, all plans will be optimized to reflect NOIs constraints of RMAS or local institutional standards & guidelines. RMAS guidelines NOIs constraints for all fractionation schemes are provided in the Supplement. The treating physician must state their intended radiation technique, number of fractions, coverage of lymph nodes, use of adaptive RT, and plan for spacer prior to randomization. Systemic therapy (e.g., ADT) is allowed at discretion of the treating physician, who must state the intended medications and duration prior to randomization (see Supplement).

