### Study endpoints

•Primary Endpoint: physician-reported, all-attribution acute GI or GU grade ≥2 adverse events. Adverse events will be defined using CTCAE version 5.0 grading. This study will evaluate the relative merits of standard dose RT and image-guided tumor-focused RT in terms of safety, patient-reported outcomes, and oncologic efficacy.•Secondary Endpoints:oAcute radiation-attribution GU/GI grade ≥2 adverse events.oAcute radiation-attribution grade ≥2 GU adverse events, other than alpha blockers.oAcute any-attribution and radiation-attribution grade ≥3 GU/GI adverse events.oLate any attribution and radiation-attribution grade ≥2 and grade ≥3 GU/GI adverse events.oPatient-reported urinary and bowel quality of life, defined as a decrease of 7 points and 6 points on the irritative/obstructive and bowel domains, respectively, of EPIC-26 at 3 months, 6 months, 12, 18, and 24 months after completion of RT.oBiochemical recurrence free survival at 5 years, defined as the percentage of participants alive and without biochemical at 5 years after completion of RT.oLocal failure at 5 years, defined as the percentage of participants with intra-prostatic recurrence (as assessed by MRI and/or PSMA PET/CT or via confirmatory biopsy after biochemical recurrence) at 5 years after completion of RT.oDistant-metastasis-free survival at 5 years, defined as absence of local or regional lymph node recurrence (as confirmed on imaging including PSMA PET/CT and mpMRI) at 5 years after completion of RT.oOverall survival at 5 years, defined as the percentage of patients alive at 5 years after completion of RT.

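### The seminal vesicle extent is worded differently in the two arms, and vesicle coverage is not among the items listed for declaration before randomization

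*Protocol article*

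**What the plan says.** - **Experimental arm:** the low-dose clinical target volume is the "prostate +/- seminal vesicles (at the discretion of the treating physician"). How much of the vesicles may be covered is not stated.
- **Control arm:** "The proximal seminal vesicles may be included at physician discretion and would receive the *CTV_low* dose in Table 2". The whole prostate receives the full prescription.
- **Both arms:** "all other CTV and PTV structures should conform to RMAS or local institutional standards and guidelines". The same section lists what the physician must state before randomization: technique, number of fractions, lymph node coverage, adaptive treatment and spacer plan, together with intended systemic therapy. Seminal vesicle coverage is not named.
- **Design:** the reason for declaring the plan in advance is given. "To minimize biased clinical decision-making based on randomization, treating physicians will declare" the plan before allocation is known. The balancing factors are risk group, fractionation type, ADT duration, bladder filling and spacer use.
- **Treatment description:** the intervention is ablative dose to tumor while "de-escalating dose to areas of subclinical disease or benign prostate tissue within the rest of the electively irradiated prostate".
- **Study endpoints:** the primary endpoint is physician-reported, "all-attribution acute GI or GU grade ≥2 adverse events".

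**The concern.** Apart from the tested contrast, the arms should be planned by the same rules. That contrast is tumor boost with a lower dose to the rest of the prostate, and how far up the seminal vesicles the elective volume extends is no part of it. Yet the two arm descriptions address the same optional structure, at the same dose level, in different words: one gives no extent and the other names the proximal part.

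The vesicles lie near the rectum and bladder, and the protocol's Introduction says that side effects are driven by dose to neighboring organs, those two in particular. The physician who draws the volumes has to plan to the assigned arm and so knows it. If vesicle coverage is settled at that stage, under arm-specific wording, elective volume could differ between arms for reasons unrelated to the research question. The randomized comparison of acute GU/GI events would then include that difference along with the intended one.

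**Working it through.** The plan gives no figure for this point, so the check compares the text of the two arms.

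**1. Extent and dose by arm**

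| Item | Experimental arm | Control arm |
|---|---|---|
| Vesicles named | Seminal vesicles, no extent given | Proximal seminal vesicles |
| Inclusion | Optional, physician's discretion | Optional, physician's discretion |
| Dose if included | CTV_low | CTV_low |

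Inclusion rule and dose level agree. Only the named extent differs.

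**2. The dose attached to this volume.** The CTV_low column of Table 2 gives 56 Gy in 28 fractions for the 39–40 fraction row, 56 Gy for the 28 fraction row, 56 Gy for the 20 fraction row and 30 Gy for the 5 fraction row. The 5 fraction row reads "D98 up to 45 Gy 40 Gy 30 Gy 25 Gy" across GTV, CTV_high, CTV_low and CTV_LN. Vesicle beyond the proximal part, if included, would therefore be prescribed 56 Gy or 30 Gy in the experimental arm. The control-arm text gives that part no prescription. This describes what the wording permits; it is not an effect size.

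**3. Does any shared rule settle the extent?** The Both arms section sends other target volumes to departmental or local standards. Both arm descriptions already address the vesicles, so it is unclear whether vesicle extent counts as one of the others. Even if it does, the article states no common extent. The Experimental arm section invokes departmental standards for creating planning target volumes, and leaves vesicle inclusion in CTV_low to the physician.

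**4. Is the choice fixed before allocation?** The Design section asks for the treatment plan in general terms. The itemized list in the Both arms section includes one elective volume, the lymph nodes, and omits the other, the vesicles. Vesicle coverage is not a balancing factor either, although risk group is.

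**5. Can an effect on the endpoint be calculated?** That would need the vesicle extent treated in each arm, the inclusion rate in each arm, and a link from the added volume to grade ≥2 events. The document gives none of these. The planning rates of 40% and 25% do not help, because they carry no information on vesicle volume.

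**The case against.** The strongest reply is that the control-arm sentence is permissive. It says that the proximal vesicles may be included; it does not say that nothing else may be. The same section describes the trial as not overly prescriptive for controls and ties their treatment to departmental or local practice. Vesicle beyond the proximal part could thus be read as one of the other structures governed by those standards. The experimental wording does not require whole-vesicle coverage either. The article is also a condensed account: the word proximal may have been dropped in shortening, and the departmental standard may give one extent for everyone.

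Most of this stands. A reader might infer that controls are capped at the proximal vesicles while experimental patients are not, so that any extra volume must fall in the experimental arm and work against it. The documents do not support that reading: there is no cap in the control text, and discretion runs in both arms, so even the direction is open. A reader might also infer that treated volumes will differ, and nothing shown establishes that.

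Existing safeguards also narrow the risk. The arms are balanced on risk group, a plausible driver of vesicle coverage. Normal-organ constraints and peer review of plans apply to both arms. The general declaration in the Design section may in practice include the vesicles.

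What the reply does not remove is that the article states a vesicle rule for each arm, and the two differ. This is an inconsistency in stated text, not a detail left to a fuller document. Nor does the reply explain why the itemized list names nodes and leaves out vesicles.

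**Conclusion.** The point holds as a cheap improvement and does not threaten the primary comparison. The arm descriptions differ in the vesicle extent they name, no text shown makes the rule common, and the listed declarations do not cover the choice. A physician who knows the arm can therefore decide on a discretionary volume near the rectum and bladder in a trial judged on acute GU/GI events.

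The direction and size of any effect cannot be computed from the document. The effect is probably small, since inclusion is optional, the dose when included is the same in both arms, and the same planning constraints and peer review apply. No sample size, test or stated figure changes.

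The conclusion rests on two assumptions: that the physician knows the arm when contouring, which follows from the different target definitions, and that no unseen departmental standard already imposes one extent in both arms. If such a standard exists, what remains is a wording correction and the gap in the declaration list.

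**What to change.** 1. Use the same vesicle extent wording in both arm descriptions: proximal in both, or the same clinically indicated extent in both, for example by risk group or vesicle involvement. If a departmental standard already fixes the extent, cite it in both places.
2. Add intended seminal vesicle coverage and extent to the items that the physician must state before randomization, next to lymph node coverage.

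The cost is an edit to the two arm descriptions, one more declared item per participant, and slightly less flexibility for the physician. Clinical discretion is kept, but it is exercised before the arm is known, which is the purpose the Design section gives for declaring the plan in advance.
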